## Abstract

**Background:**

Dizziness is a very common symptom that often leads to reduced quality of life, anxiety and emotional distress, loss of fitness, lack of confidence in balance, unsteadiness and an increased risk of falling. Most dizzy patients are managed in primary care by reassurance and medication to suppress symptoms. Trials have shown that chronic dizziness can be treated effectively in primary care using a self-help booklet to teach patients vestibular rehabilitation exercises that promote neurological adaptation and skill and confidence in balance. However, brief support from a trained nurse was provided in these trials, and this model of managing dizzy patients has not been taken up due to a lack of skills and resources in primary care. The aim of this trial is to evaluate two new alternative models of delivery that may be more feasible and cost-effective.

**Methods/Design:**

In a single blind two-centre pragmatic controlled trial, we will randomise 330 patients from 30 practices to a) self-help booklet with telephone support from a vestibular therapist, b) self-help booklet alone, c) routine medical care. Symptoms, disability, handicap and quality of life will be assessed by validated questionnaires administered by post at baseline, immediately post-treatment (3 months), and at one year follow-up. The study is powered to test our primary hypothesis, that the self-help booklet with telephone support will be more effective than routine care. We will also explore the effectiveness of the booklet without any support, and calculate the costs of treatment in each arm.

**Discussion:**

If our trial indicates that patients can cost-effectively manage their dizziness in primary care, then it can be easily rolled out to relieve the symptoms of the many patients in primary care who currently have chronic, untreated, disabling dizziness. Treatment in primary care may reduce the development of psychological and physical sequelae that cause handicap and require treatment. There is also the potential to reduce the cost to the NHS of treating dizziness by reducing demand for referral to secondary care for specialist assessment and treatment.

**Trial Registration:**

ClinicalTrials.gov trial registration ID number: NCT00732797

## Background

Dizziness has a prevalence of up to 25% in the community [1-4], and 1 in 10 working age adults report some degree of handicap due to dizziness [3]. Dizziness is a more severe problem for older people; more than 1 in 5 people aged over 60 have current dizziness that has led to significant disability, medical consultation or medication use [5]. Dizziness is also associated with falls, fear of falling and loss of independence in older people [6,7].

The most common cause of dizziness in primary care is peripheral vestibular disorder, and serious sinister pathology in patients with no other symptoms is very rare [2,8-12]. Most patients are therefore managed in primary care [1,9,13,14] by reassurance and medication for symptomatic relief [9,11,13,15,16]. However, living with chronic dizziness often entails avoiding all physical activities and situations that might provoke dizziness, leading to clinically significant limitations in physical functioning, reduced quality of life, emotional distress, loss of fitness, unsteadiness and lack of confidence in balance (especially as patients get older), and vulnerability to falling [17-20]. Anxiety about symptoms can contribute to this vicious cycle of chronic dizziness and distress, and a significant minority of patients develop secondary symptoms of panic and agoraphobia [21,22]. Moreover, reviews of the management of dizziness have concluded that no medication has well-established value or is suitable for long-term use, and vestibular rehabilitation (VR) is now recommended as the treatment of choice [11,16,23-27].

VR involves the patient carrying out graded exercises for 10-20 minutes daily for 6 to 12 weeks, consisting of specific eye, head and body movements that stimulate the vestibular system so as to promote neurological adaptation to the altered input from the damaged labyrinth [15,28,29]. Performing these exercises also helps patients to overcome fear and avoidance of activities that provoke dizziness, and regain skill and confidence in balance, reducing the risk of falls [30,31]. Small scale studies have provided some evidence that VR may be an effective treatment for dizziness due to a variety of conditions, including peripheral and central vestibular disorder, benign paroxysmal positional vertigo, whiplash-associated dizziness, acute vertigo, surgery for acoustic neuroma, anxiety, head injury, and dizziness in the elderly [32-40]. A Cochrane review of 21 randomised clinical trials of VR for dizziness due to a range of unilateral peripheral vestibular disorders reported that almost all the trials included in the review demonstrated that VR was a more effective treatment for dizziness than other interventions [25].

Access to VR in the UK usually involves referral to secondary care for a consultation and neuro-otological assessment, often followed by referral to a physiotherapist for VR. Between 9% and 19% of dizzy patients are currently referred to secondary care [1,13]. Two trials, however, have shown that chronic dizziness can also be treated effectively in primary care, using a self-help booklet that instructs patients how to carry out VR with brief support from a trained nurse [41,42]. A non-blind randomized controlled trial provided a preliminary positive evaluation of the efficacy of providing the booklet together with two visits from a trained nurse [41]. The second study was a single blind randomised pragmatic trial of the effectiveness of the booklet, supported by a single session of rehabilitation delivered by nurses working in primary care and two follow-up phone calls [42]. Patients with chronic dizziness from 20 practices were randomised to VR (n = 83) or usual medical care (n = 87). Post-treatment, improvement in the treatment group was significantly greater than in the usual medical care group on all primary outcome measures (including reported symptoms, disability and handicap and objective measurement of postural stability), and was maintained at six months; 67% of treated patients reported clinically significant improvement, compared with 38% controls (relative risk = 1.78, 95% C.I. 1.31 to 2.42). Nearly four times as many treated patients as controls had no provoked symptoms at all. These results are comparable to those achieved in secondary care [25,27].

A further study has investigated whether the booklets are effective if no support is provided [43]. The study was carried out in a sample of people with Ménière's disease, a severe and recurrent form of vestibular disorder for which VR can only provide temporary relief from residual dizziness in between spontaneous attacks of symptoms. Nevertheless, at 6-month follow-up, 45 (37.5%) of the VR group reported improvement compared with 19 (15.8%) controls; the relative probability of improvement compared with controls was 2.37 (95% C.I. 1.48 -3.80). Post-treatment, the rehabilitation group had reduced symptoms, anxiety, handicap, and negative beliefs about dizziness, while the control group showed no improvement. However, reported adherence levels were low and strongly related to outcome. Giving patients the means to manage their symptoms of dizziness in primary care is consistent with the Department of Health initiative to encourage self-care [44] where this can bring benefit to patients and savings for the NHS.

### Rationale and aims

Despite the consensus that VR is the treatment of choice for patients with dizziness of peripheral vestibular origin [23,27], few eligible patients are currently offered VR. Only 2% to 13% of dizzy patients seen by GPs eventually receive VR, of whom around 70% are seen in ENT [1,13]. Yardley and colleagues [42] found that only 3% of participants (5/170) had previously been offered VR, despite a mean duration of dizziness of 8 years, yet 2/3 of participants benefited from it. Although it has been demonstrated that the self-help booklet is effective when combined with support from a practice nurse, this model of managing dizzy patients has not been taken up in primary care due to a lack of skills and resources. The primary aim of the current trial is to determine whether VR can be delivered to dizzy patients in primary care in a feasible, safe and cost-effective way. Two new alternative models of delivery of VR in primary care will be evaluated that may be more feasible and cost-effective.

The first model will examine whether using the self-help booklet with telephone support from a vestibular therapist can be effective. This model of delivery is more feasible than the previous model to roll out across the NHS, as there are already many trained vestibular therapists currently providing therapy in secondary care, whereas very few general practices can provide expert support for VR. Patients may also benefit from having support from an expert vestibular therapist rather than a nurse with limited training. However, remote support from an unknown person might be less effective than close contact with a familiar nurse. The cost of referring patients to secondary care for diagnostic evaluation prior to VR is substantial. The cost varies widely depending on the procedures undertaken, but for patients referred for VR are likely to average around £250 (this figure is based on typical costs of a medical consultation with a senior hospital doctor [45], and the cost of a vestibular assessment and one session of rehabilitation). Expert telephone support for VR can be provided for around £40 an hour (since typical costs for physiotherapists and similar health professionals are no more than £35/hour [45]). Consequently, using our new proposed model of delivery, it should be possible to provide six primary care patients with VR with expert telephone support for less than the cost of referring one patient to secondary care for VR. We predict that by providing treatment and expert support in primary care, the number of patients requiring referral will be reduced, resulting in a lower cost of managing dizziness.

Having previously demonstrated that the self-help booklet alone has a small effect on symptoms and handicap in people with Ménière's disease [43], our second model predicts that it will also be effective in a primary care sample of patients with less severe, recurrent symptoms. In the previous trial, over a third of patients were able to successfully self-treat using the booklet without support. The cost of providing only the self-help VR booklet to patients in primary care is negligible (less than 50 p), and is comparable to the cost of a single prescription of the types of medication commonly used for dizziness symptoms. Since this is a very low cost model of delivery it may well prove cost-effective if a similar proportion of patients benefit from it, and even if only a small proportion of patients can be managed in primary care by the self-help booklet alone, this may still result in substantial savings for the NHS. Because the effect size of using the booklet alone is likely to be small we are unable to power the trial for a definitive test of this hypothesis, but this study will allow us to estimate the likely treatment effect size in a primary care population (which has not yet been established), which would permit a definitive trial in the future.

Provision of the self-help booklet (either with or without telephone support) may therefore represent a cost-effective first stage of patient management, reserving referral to secondary care for patients who require further assessment and therapeutic input.

• Hypothesis 1: Provision of a self-help booklet teaching VR exercises, with up to one hour of telephone support from a vestibular therapist, will be a) more effective than routine care in reducing symptoms (and therefore also disability and handicap) in dizzy patients in primary care, and b) less costly than routine care of dizzy patients.

• Hypothesis 2: Provision of a self-help booklet teaching VR exercises, without any other support, will be a) more effective than routine care in reducing symptoms (and therefore also disability and handicap) in dizzy patients in primary care, and b) less costly than routine care of dizzy patients.

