#### Inclusion criteria

a) Patients must be 18 or over and registered at a participating general practice.

b) Patients must have seen their GP for dizziness some time in the past two years (Participating practice computerised databases will be searched using search terms such as: vertigo; dizziness; Meniere's disease; balance problems; vestibular; prochlorperazine; cinnarizine; betahistine; diuretics - terms used will vary according to how patient data is recorded by the practice).

c) Patients must return the completed and signed consent form

d) Patients must indicate in the baseline questionnaire assessment that they still experience dizziness and that quick head movements make them dizzy.

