#### Exclusion criteria

a) Non-labyrinthine cause of dizziness identified by GP (in which case patients will not benefit from the vestibular rehabilitation exercises)

b) Medical contraindications for making normal head movements (e.g. severe cervical disorder), in which case patients will be unable to carry out the exercises.

c) Serious co-morbidity (e.g. progressive central disorder, terminal illness, and moderate to severe dementia or mental illness).

d) Moved away from practice

e) Recently deceased

f) Non-English speakers and people unable to read and write English.

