#### Cost -effectiveness analyses

For the cost-effectiveness analyses, the EuroQol - EQ-5D data will be converted to utility values using the published national tariff. Incremental cost effectiveness ratio (ICER) data will be estimated. Cost effectiveness acceptability analysis will quantify the level of uncertainty in stochastic data. Sensitivity analysis will test the structural uncertainty in a simple model. To determine the probability that one intervention is cost effective relative to the other, we will examine bootstrapped estimates of imputed mean costs, the cost effectiveness plane of the incremental cost effectiveness ratio, net benefit statistics and cost acceptability curves. As in the clinical outcome analyses, these analyses will be adjusted to control for the effect of any clinically significant difference between the groups on baseline variables.

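### Cost comparisons should always be adjusted for baseline dizziness-related resource use, including prior referral, and not only when the arms appear to differ

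*Protocol article*

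**What the plan says.** **Why cost should fall.** Under Rationale and aims the article gives its mechanism: "We predict that by providing treatment and expert support in primary care, the number of patients requiring referral will be reduced". It adds that the booklet "may therefore represent a cost-effective first stage of patient management, reserving referral to secondary care for patients who require further assessment". Hypotheses 1b and 2b then state that each booklet arm will cost less than routine care of dizzy patients in primary care.

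**Who enters.** The inclusion criterion on care history is "Patients must have seen their GP for dizziness some time in the past two years". The practice search terms include established diagnoses: "vertigo; dizziness; Meniere's disease; balance problems; vestibular; prochlorperazine; cinnarizine; betahistine; diuretics". The exclusions begin with "Non-labyrinthine cause of dizziness identified by GP (in which case patients will not benefit from the vestibular rehabilitation exercises"; none of the six concerns earlier or pending referral, or earlier vestibular rehabilitation (VR).

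**What is recorded.** Table 1 lists management of dizziness (primary and secondary care consultations, hospital stays, treatment, days off work) at baseline and again at one year. The text under Outcome measures adds previous referrals to the baseline record.

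**How it is used.** Under Primary and secondary analysis, every clinical outcome is adjusted for its own baseline level, and additionally for variables that differ by chance. Under Cost-effectiveness analyses the only stated rule is that the analyses are "adjusted to control for the effect of any clinically significant difference between the groups on baseline variables".

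**The concern.** Two features of the cost rule are weak.

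First, it is conditional on the data. Whether baseline management enters the model is settled only after the arms have been compared, against a threshold of clinical significance that the article does not define. Clinical significance is also an awkward yardstick for a cost covariate.

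Second, it ties adjustment to the wrong condition. Past use of care is a likely predictor of later use. Someone already under a specialist may well generate secondary care cost in the follow-up year whichever arm they are in. Adjusting for such a variable sharpens the comparison whether or not the arms differ on it. When they look balanced, the stated rule gives that gain away.

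At stake is the precision of the estimates for hypotheses 1b and 2b, and whether the cost estimator is settled before the data are seen.

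**Working it through.** **1. The plan's own figure.** With d = 0.41, two-sided 5% and 80% power: n = 2 × (1.960 + 0.842)² / 0.41² = 93.4, rounded up to 94 per group. The t-based version gives 94.35, rounded up to 95, as stated; power at 95 is 80.7%. This concerns symptoms at 3 months and is not touched by the cost adjustment. The article gives no corresponding figure for cost.

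**2. The two rules side by side.**

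| | Clinical outcomes | Costs |
|---|---|---|
| Own baseline level | Always adjusted | No such rule stated |
| Other baseline variables | Adjusted if they differ by chance | Adjusted if they differ to a clinically significant degree |
| Baseline data collected | Yes (Table 1) | Yes (Table 1) |

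The cost section says that it follows the clinical analyses, but what it carries over is only the second row.

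**3. What fixed adjustment gains.** For a linear model with one baseline covariate, Var(adjusted difference) ≈ (1 − ρ²) × Var(unadjusted difference), where ρ is the within-arm correlation of baseline with follow-up cost. The observed imbalance is not what produces the gain; ρ is. The article gives no ρ, so I put no number on it.

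**4. Scale of chance imbalance (illustration).** The article does not give the share of participants referred before entry. It says "Between 9% and 19% of dizzy patients are currently referred to secondary care". Assume that this range applies to participants; it is a rate among dizzy patients and not a measured share of this sample.

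- Expected number per arm: 110 × 0.09 = 9.9 and 110 × 0.19 = 20.9, so about 10 to 21.
- Standard error of the difference in shares between two arms, √(2p(1 − p)/110): √(2 × 0.09 × 0.91 / 110) = 0.0386 and √(2 × 0.19 × 0.81 / 110) = 0.0529.
- In patients: 110 × 0.0386 = 4.2 and 110 × 0.0529 = 5.8.

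Randomisation is stratified by practice and symptom severity, not by prior referral, so differences of this order are ordinary. If, purely for scale, each previously referred participant cost £250 more in the follow-up year (the article's approximate cost of one referral for VR), one standard error of imbalance would move the difference in mean cost by 250 × 0.0386 = £9.6 to 250 × 0.0529 = £13.2 per patient. The article prices telephone support at about £40 per hour, with up to one hour planned. A smaller excess cost shrinks the shift in proportion. An imbalance of four to six patients could be judged clinically significant or not; the rule does not say.

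**The case against.** **On the rule itself.** The statistician stays blind to allocation, which limits any steering of covariate choice. An article may also leave cost covariates to a fuller plan. Both are fair. But this article does state a rule, and the rule is conditional; blinding does not make it fixed, nor recover the precision.

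**Stronger readings that a reader might infer.** The documents do not support these:

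- *Referral can no longer be avoided in patients already referred.* Referrals and costs are counted over the follow-up year, when new or repeat referrals can still be averted. Total cost also covers primary care consultations and treatment.
- *The wrong population is enrolled, so prior VR should be excluded or the cost contrast confined to never-referred patients.* The hypotheses concern dizzy patients in primary care, with no restriction to first presentation. The design is pragmatic and was chosen for comparability with the previous trial. Either change would trade that away.
- *Prior VR dilutes d from 0.41 to 0.40–0.36.* This multiplies 0.41 by 1 − 0.02 and 1 − 0.13, using "Only 2% to 13% of dizzy patients seen by GPs eventually receive VR". That is eventual receipt, not VR before entry. The d = 0.41 also comes from a trial in which 5 of 170 (3%) had already been offered VR, so dilution at that level is already inside it. Nor does dizziness after earlier VR show failure: in Ménière's disease the article itself says relief is only temporary.
- *Break-even at 40/250 = 16 averted referrals per 100 measures the problem.* That sum would be the same if nobody had been referred before, it leaves out other costs, and it does not fit the booklet-alone arm, where the booklet costs under 50p.

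**Conclusion.** The point holds as an improvement available at no cost, not as a flaw in eligibility. The cost section makes adjustment depend on observed differences and sets no fixed baseline term, although the data are collected and clinical outcomes always receive one.

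There is no bias between arms: individual randomisation balances prior care in expectation, and an unadjusted comparison remains valid. The 3-month symptom analysis is unaffected.

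The loss is precision, by a variance factor of about 1 − ρ² that the article does not allow one to size, together with an estimator that is not fixed in advance. The conclusion rests on one assumption, that earlier dizziness-related care predicts later cost. That is likely, but not shown in the article. If ρ were near zero the gain would be small, and adjustment would cost almost nothing.

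**What to change.** In Cost-effectiveness analyses, replace the conditional rule with a fixed one: every cost comparison under hypotheses 1b and 2b is adjusted for baseline dizziness-related resource use or cost, including prior referral (yes/no), whether or not the arms differ. Fit the adjustment within each bootstrap resample so that it carries through to the net benefit and acceptability results.

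Keep all randomised patients as the primary cost comparison. A result by prior referral may be reported as a secondary description, without a claim of power.

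The cost is a sentence or two in the plan and one or two model terms. Eligibility, sample size and data collection stay as they are. Participants with an incomplete baseline management item will need a stated handling rule so that none drop out of the primary cost comparison.

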## Methods/Design

### Design overview

A single blind two-centre pragmatic randomized controlled trial design will be used to compare the effectiveness and cost-effectiveness of a) the self-help booklet with expert telephone support and b) routine care (see Figure 1 for flow diagram of the trial design). We will also evaluate the effectiveness and cost-effectiveness of providing the self-help booklet alone compared with routine care. Participants who receive the self-help booklet (with and without support) will be asked to carry out the exercises in the booklet for up to 12 weeks. We will calculate the total costs of treatment in each arm, including costs of the interventions, primary care consultations and treatment, secondary care consultations, assessment and treatment. Symptoms, disability and handicap will be assessed by validated questionnaires at baseline, 12 weeks after allocation to treatment group, and at one year follow-up. We will compare the change in symptoms and quality of life and the total costs of treatment in each group of patients. This design was chosen so it can be compared with a previous successful trial [42], and if found to be effective, these models of delivery can be easily rolled out through the NHS across the region and the UK.

